### Data Collection

The multiprofessional staff (i.e., neurologists, neurophysiologists, physiatrists, internists, neuropsychologists, neurophysiological technicians, nutritionists, physiotherapists, speech therapists, occupational therapists, and nurses) of each center will gather clinical and neurophysiological data and structural indices of overall brain damage from brain imaging. To promote a training on specific datasets, the coordinating center will schedule meetings with all the involved users, before the starting of the enrollment, to guarantee homogeneity of data collection. For the analysis of genetic or epigenetic markers, in the presence of signed informed consent, a blood sample will be collected from each patient along with the routine blood drawn at T0, T1, and T2, frozen and later transported to the Neurogenetics Laboratory of Careggi Hospital, in Firenze.

Measures will be taken at (1) inpatient rehabilitation admission (T0), (2) 3 months from T0 (T1), (3) 6 months from T0 (T2), (4) 12 months from the acute event (T3), and (5) 24 months from the acute event (T4). The timeline of the study is illustrated in Figure 1.

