**Statistics:**

Advanced machine learning algorithms will be cross validated to achieve data-driven prediction models. To assess the clinical applicability of the solutions obtained, the prediction of recovery milestones will be compared to the evaluation of a multiprofessional, interdisciplinary rehabilitation team, performed within 2 weeks from admission.

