**Conclusions:**

The application and validation of machine learning algorithms on a comprehensive pool of clinical, genetic, and neurophysiological data can pave the way toward the implementation of tools in support of the clinical prognosis for the rehabilitation pathways of patients after sABI.

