#### Analysis of Genetic Marker

For the subgroup of patients who will sign a further, dedicated informed consent, a blood sample, along with the routine blood drawn at T0, T1, and T2, will be frozen and sent to the University Hospital Neurogenetic Lab of Florence.

Genomic DNA will be obtained from EDTA-whole venous blood samples by Automated Systems QiaCube (Qiagen). The genetic analysis of five different single-nucleotide polymorphisms on APOE and BDNF will be performed by high-resolution melt (HRM) analyses and direct sequencing on automatic genetic analyzer. ApoE genotypes will be investigated by HRM with two sets of PCR primers designed to amplify the regions encompassing rs7412 [NC_000019.9: g.45412079C>T] and rs429358 (NC_000019.9: g.45411941T>C). The samples with known ApoE genotypes, which have been validated by DNA sequencing, will be used as standard references. Analysis of DNA methylation (DNAm) levels of BDNF will be performed according to the following protocol: equal amounts of a genomic DNA sample will be put in four separate tubes into which buffer and the appropriate restriction enzyme combinations added to detect different methylated DNA fractions. The product of a mock digest (Mo) contains all of the input genomic DNA. The product of the methylation-sensitive restriction enzyme mixture (enzyme A) digest (Ms) contains methylated DNA sequences, whereas the product of the methylation-dependent restriction enzyme mixture (enzyme B) digest (Md) contains unmethylated DNA sequences. The product of a double digest (Msd) measures the background and the success of both enzymatic digestions. To analyze the amount of DNA in each digest of each sample and determine the methylation status of CpG islands in gene promoters, all the aliquots will be amplified by a real-time PCR (Rotor-Gene 6000 Corbett Research). The analysis of the BDNF rs6265 will be performed by HRM using the following PCR primers 5′- ACTCTGGAGAGCGTGAATGG-3′ and 5′-ACTACTGAGCATCACCCTGGA-3′. The three genotypes will be identified through sequencing (SEQStudio Automatic Genetic Analyzer Life Technologies). The methylation levels of the gene promoters will be analyzed by the Epitec II DNA Methylation Enzyme Kit (QIAGEN). The genetic polymorphism data will be compared to sex- and age-matched controls of the DNA banking of the neurogenetic laboratory.

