A further step will involve advanced machine learning methods for the short- and long-term prediction of outcomes. Classical solutions such as linear and logistic regression will be compared with solutions based on support vector machines, random forests, or multilayer perceptrons and also with “deep” artificial neural networks (convolutional neural networks, recurrent neural networks, and ensemble learning solutions). The performances of different algorithms in predicting recovery outcomes will be compared in terms of accuracy, F1-score, root mean square error, and determination coefficient. The effect of hyperparameter tuning and automatic features selection strategies will also be tested by nested crossvalidation, with the final aim to quantify the solution generalization capability when applied to new patients who were not included in model definition and training.

To assess the clinical applicability of these solutions, the prediction of recovery milestones by automatic methodologies will be compared to the evaluation of a multidisciplinary team, which will be kept blind with respect to the algorithm outputs. This assessment is usually performed in clinical practice approximately 2 weeks from admission to inform the caregivers of the patients' expected recovery path. Opinions by both single professionals and the full consensus will be compared to the automatic tool predictions.

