Regarding genetic factors, a significant association of ApoE polymorphism was found with poor recovery from a posttraumatic coma (57) and, lately, with the diagnosis of prolonged UWS (58). In some studies, E4 carriers have shown longer recovery and poor outcomes by 6 months following traumatic brain injuries (7, 8). In this study, the ApoE genotype will be investigated to explore its possible effect on the functional (including motor and cognitive aspects) and participation outcomes in sABI survivors. As for BDNF polymorphism, many studies analyzed the interaction of the V66M in brain injury, with contrasting findings (59, 60). However, BDNF gene expression is complex, and nine functional promoters confer tissue and brain region-specific expression (61). For that reason, it is crucial to explore methylation levels of BDNF to analyze its expression. COMT is one of the several enzymes that degrade catecholaminergic neurotransmitters. Catecholamines are thought to play a role in recovery and functioning after traumatic brain injury (62) and variation in the metabolism of catecholamines after injury may influence cognitive function and outcome (23). Because of the biological implications of the COMT, genetic variation (methionine to valine substitution at codon 158 leads to differing enzyme activity) on catecholamine metabolism genotypes associated with lower or higher levels of catecholamines will be examined concerning the sABI recovery. Many different clinical outcomes following sABI could be influenced by these genetic factors or modulated by environmental factors that could alter gene expression by epigenetic mechanisms, such as DNA methylation (DNAm). These changes may be rapid and dynamic, and although the field of epigenetics is now well established, interest in the epigenetic mechanisms involved in sABI pathophysiology and outcome has only recently emerged (63). Moreover, knowledge of the role of epigenetic changes associated with neural plasticity, learning, and memory reinforces the idea that these mechanisms could influence the consequences of brain injury, the recovery and the response to therapies, providing innovative approaches to sABI recovery and rehabilitation. In this study, it will be analyzed if there is a possible correlation between methylation levels of BDNF and DNA damage-inducible (Gadd) 45 protein (GADD45) genes and clinical outcome after sABI. GADD45 proteins act through a variety of molecular signaling cascades, including the cell-cycle control mechanisms, histone regulation, and epigenetic DNA demethylation. It will be of interest to evaluate methylation levels of these two genes in the recruited patients at the time of admission and 3 and 6 months after the event. Understanding the influence of individual epigenetic patterns on the intensive rehabilitation functioning after sABI may open new perspectives on the rehabilitation pathways.

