
To identify a profile of sABI patients based on a multiparameter assessment, the combination of the many recorded measures can be best exploited by machine learning analysis. The applicability of these solutions is also supported by the consideration that, with the only exception of the neurogenetic assessment, all the clinical and instrumental variables selected in this study are easily exportable to other clinical realities because of their low cost and high feasibility. Specifically, in this context, an accurate prediction is relevant both for planning a personalized rehabilitation pathway and for communication with relatives and caregivers. For these reasons, the ultimate goal of this study is to reliably predict the main recovery milestones, including the achievement of a consciousness recovery, tracheostomy decannulation, complete oral nutrition, functional independence, and the recovery of participation in familiar and social contexts. Differently from what is most often found in the existing literature, the aim of these analyses will be two-fold, addressing both the success in the achievement of these goals and their timing. The candidate predictors of these solutions will be selected from a comprehensive evaluation of sABI patients, including the biomarkers obtained from genetic sequencing and quantitative and qualitative EEG features.

Finally, another innovative point will be the comparison of these models with the clinical assessment performed by a multidisciplinary team within the first 2 weeks from admission. This comparison will represent a first step in the direction of computational tools translation into clinical practice.

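### The algorithm set against the team's two-week forecast has genetic markers among its candidate predictors, and nothing limits it to data in hand at that forecast

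*Protocol article*

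**What the plan says.** **The comparison.** The Abstract (Statistics) says that the prediction of recovery milestones "will be compared to the evaluation of a multiprofessional, interdisciplinary rehabilitation team, performed within 2 weeks from admission". The Statistical Analysis section gives the purpose as assessing clinical applicability: "the prediction of recovery milestones by automatic methodologies will be compared to the evaluation of a multidisciplinary team". It puts the team's assessment at approximately two weeks from admission and keeps the team blind to the algorithms' outputs.

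**The inputs.** The Discussion states: "The candidate predictors of these solutions will be selected from a comprehensive evaluation of sABI patients, including the biomarkers obtained from genetic sequencing", together with EEG features. The Abstract (Conclusions) describes the same pool: "The application and validation of machine learning algorithms on a comprehensive pool of clinical, genetic, and neurophysiological data".

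**The genetic samples.** Under Data Collection, blood drawn at T0, T1 and T2 is "frozen and later transported to the Neurogenetics Laboratory of Careggi Hospital, in Firenze". Under Analysis of Genetic Marker, it is taken "For the subgroup of patients who will sign a further, dedicated informed consent".

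**The exception.** The Discussion supports applicability by the low cost and high feasibility of the chosen variables, and excludes only the neurogenetic assessment from that claim. Its last paragraph says that profiling will include measures readily obtained at the bedside, and does not repeat the exception.

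**The concern.** The comparison with the team is the article's own test of whether the tool is usable in practice. The forecast is made at a fixed moment, so the test is informative about the tool only if the tool's inputs could be in hand at that moment. The article fixes the moment and names genetic markers as candidate inputs, but does not connect the two.

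If a model that retained genetic features did better than the team, two explanations could not be separated: the algorithm used the available information better, or it had information the team did not have. The result would also concern a model containing the one component that the authors exclude from easy transfer to other centres. The tool they describe as low-cost and feasible would remain untested against clinicians.

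**Working it through.** The point depends on no sample size, power or significance level, and the article gives no figure for this comparison that could be reproduced. The check is to set the statements side by side.

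| Step | Where | What it establishes |
|---|---|---|
| 1 | Statistical Analysis; Abstract, Statistics | The algorithms are compared with a team forecast at about, or within, two weeks of admission, in order to judge applicability |
| 2 | Discussion; Abstract, Conclusions | Genetic sequencing results are candidate predictors of those algorithms |
| 3 | Data Collection | Genetic samples are frozen and shipped later to one laboratory; no turnaround is given |
| 4 | Analysis of Genetic Marker | Only patients with a separate consent have genetic data |
| 5 | Discussion | Neurogenetics is the only assessment excluded from easy transfer |
| 6 | Statistical Analysis | The one stated safeguard is that the team does not see the algorithms' outputs |

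**Timing of the other inputs.** Neurophysiological tests are done within one week of admission (Neurophysiological Assessment). The CRS-R value is the best of five administrations in seven days (Clinical Evaluation). Both fit a forecast at two weeks. For genetics the article gives no comparable timing.

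**Whether another provision closes the gap.** Blinding the team keeps the algorithm from influencing the forecast, but does not align the information on the two sides. Nested cross-validation estimates how a model with given features performs in new patients. It does not ask whether a user would hold those features at the forecast. Automatic feature selection may drop the genetic variables or keep them, and the article does not say what follows if they are kept.

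**Scale, on assumptions only.** The documents give neither the share of patients who will sign the genetic consent nor the rate at which algorithm and team disagree on correctness. Assume 50% to 80% consent and 20% discordant forecasts. Under no difference, the standard error of a paired difference in accuracy is √(discordant proportion / n).

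- All patients: √(0.20/520) = 0.0196, about 2.0 percentage points.
- 80% consent: n = 0.80 × 520 = 416; √(0.20/416) = 0.0219, about 2.2 points.
- 50% consent: n = 0.50 × 520 = 260; √(0.20/260) = 0.0277, about 2.8 points.

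The two smaller samples apply only if genetic features are retained and patients without them are left out of the comparison. The article states neither. These figures say how precise a comparison in the consenting subgroup would be. They do not say how much genetics would favour the algorithm, and the documents give no basis for such an estimate.

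**The case against.** The strongest reply is that this is silence in a condensed article. Candidate predictors are not the final inputs, and which fitted model meets the team's forecast is a detail that often sits in the full protocol or analysis plan. That stands as a reason for modest weight. It does not remove the point, because the article itself names the predictors, the forecast time, the sample handling and the exception for genetics, and leaves them unreconciled.

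Second, comparing a biomarker-informed tool with usual team judgement is a legitimate question, and the predictive role of genetic polymorphisms is a stated aim in the Introduction. That also stands, and it is why the genetic model should be kept and reported, though not as the only model compared with the team.

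Third, the authors already disclose that neurogenetics is the exception, and on grounds of cost and feasibility, not timing. This is correct, but the disclosure is not carried into the comparison.

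Several stronger readings are tempting and are not supported:

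- A reader might infer that genetic results will arrive after the forecast. No section says so; the article only does not show that they will be available.
- A reader might infer leakage of future information. Genotype is fixed, and blood drawn at T0 gives a baseline measurement.
- A reader might infer that methylation feeds the algorithms. The Discussion says only "It will be of interest to evaluate methylation levels of these two genes in the recruited patients at the time of admission", and later, in connection with a possible correlation with outcome. The sentence on candidate predictors names sequencing, whereas methylation is measured by restriction digest and real-time PCR.
- A reader might infer that the comparison will shrink to the patients with genetic consent. That needs genetic features to survive selection and a complete-case analysis, and neither is stated.
- The bedside statement in the last paragraph of the Discussion says what profiling will include. It does not confine profiling to bedside measures, so it is not a flat contradiction.

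**Conclusion.** The point holds in conditional form. Genetic markers are candidate predictors of the algorithms whose applicability is tested against a two-week team forecast, and nothing limits the compared model to data in hand by then. If genetic features are retained, a result in the algorithm's favour could not be attributed to better use of the information available at the forecast, and would not show that the exportable tool is applicable.

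The size of any advantage cannot be derived from the documents. It depends on whether genetic features survive selection, how much they add, how many patients consent and how patients without genetic data are handled. The standard errors of about 2.2 to 2.8 points for a consenting subgroup rest wholly on the assumed consent and discordance rates. This is an inexpensive improvement that lets the comparison answer its own question, not a defect that invalidates the study.

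**What to change.** State in the Statistical Analysis section that the main comparison between algorithm and team uses a model trained and cross-validated in all patients on T0 variables available by the team's forecast: clinical and functional scales, CRS-R, EEG, SEP, MEP and ENG/EMG. Report the model with genetic markers separately, as added predictive value over that model in the patients who gave genetic consent. Fix this choice before the predictions are compared, so that the feature set is not chosen after the results are seen.

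The cost is one sentence and one extra model fit. The compared algorithm may score slightly lower than one with genetic inputs. No data are discarded and the genetic aim is kept.

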**Figure 1 F1:**
[figure not shown]
Study timeline.

#### Clinical Evaluation

At admission (T0), demographical and clinical data, including those related to the acute event, will be recorded. In particular, sABI etiology (posttraumatic, postanoxic, postischemic, posthemorrhagic or other), localization and extension of the brain damage, as described by brain imaging, the presence of clinical complications in the acute phase (e.g., a second brain event, acute epileptic event), treatment received during the acute phase (e.g., thrombolytic therapy, neurosurgery), and eventual procedural complications, will be recorded.

Markers of clinical and nursing complexity will be assessed at T0, T1, and T2, including the presence and severity of comorbidity as measured by the Cumulative Illness Rating Scales, the body mass index, the presence of medical devices, and pressure ulcers. At 3 months (T1) and 6 months (T2), any clinical event that occurred between the T0 and T1 and between T1 and T2, respectively, will be registered. More specifically, late epileptic event, recurrence, the presence of paroxysmal sympathetic hyperactivity (PSH), and the emergence of spasticity or heterotopic ossifications will be considered. Also, the pain will be assessed using the Nociception Coma Scale, the Numeric Rain Scale, or the pain assessment in advanced dementia scale, according to the patient's level of consciousness. Additionally, all pharmacological therapy introduced for epilepsy, PSH, spasticity, or pain, will be recorded. Past medical history, and baseline functional evaluation including measures of consciousness state, impairment and disability, administered by skilled members of the multiprofessional team, will be recorded at each time point, according to the patient's clinical state:

Level of consciousness will be assessed using the Italian version of the CRS-R. The best score obtained from five administrations performed in seven days will be recorded. When available, the lowest Glasgow Coma Scale achieved during the acute phase will be recorded.The neurocognitive and behavioral assessment will include the anamnestic Cognitive Reserve Index, the level of cognitive functioning, the Galveston Orientation and Amnesia Test, the Apathy Evaluation Scale, the Agitated Behavior Scale, the Halpern communication scale or the Goodglass–Kaplan communication scale, the Aachener Aphasie Test, the Hospital Anxiety and Depression Scale or the Aphasic Depression Rating Scale, and the Phone Montreal Cognitive Assessment.The sensorimotor impairment will be assessed by the Trunk Control Test and the modified Ashworth Scale, whereas dysphagia will be assessed using the Functional Oral Intake Scale.Disability will be measured by the Early Rehabilitation Barthel Index, the Disability Rating Scale, the Functional Independence Measure, and the Glasgow Outcome Scale-expanded (GOS-E).

After hospital discharge, at T3 and T4, a phone interview with the patients and their principal caregiver will be carried out, to evaluate their clinical state including consciousness level, disability level, dysphagia, and participation level using the Community Integration Questionnaire. The quality of life as perceived by both the patient and the caregiver will be assessed through the quality of life (QoL) after the Brain Injury Scale (QoLibri). Additionally, any relevant clinical event occurring after discharge will be recorded.

All assessment tools are summarized in Table 1, and the details on the references for each tool are reported in Supplementary Table S1.

**Table 1 T1:** Assessment tools.

**Area of competence**		**Evaluation tool**	**T0**		**T1**	**T2**	**T3**	**T4**

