							**Phone follow-up**	
			**Anamnestic evaluation**	**Baseline evaluation**	**3 months from T0**	**6 months from T0**	**12 months from onset**	**24 months from onset**
		Etiology		X				
		Brain localization and extension		X				
		Trial of Org 10172 in Acute Stroke Treatment		X				
**Acute event**		Oxfordshire Community Stroke Project		X				
		Early clinical complications		X				
		Treatment received during the acute phase (thrombolysis/fibrinolysis)		X				
		Procedure complications		X				
		Cumulative Illness Rating Scale	X	X	X	X		
		Presence of medical device		X	X	X	X	X
**Clinical complexity**		Body mass index	X	X	X	X	X	X
		Braden scale		X	X	X		
		Relevant medical complications				X	X	
		Pain assessment (NRS/NCS/PAINAD)		X	X	X		
	**Consciousness**	Glasgow Coma Scale		X				
		Coma Recovery Scale revised		X	X	X	X	X
	**Neurocognitive evaluation**	Cognitive reserve index	X					
		Level of cognitive functioning		X	X	X		
**Functional assessment**		Galveston Orientation and Amnesia Test			X	X		
		Apathy Evaluation Scale			X	X		
		Agitated Behavior Scale			X	X		
		Halpern communication scale or the Goodglass–Kaplan communication scale			X	X		
		Montreal cognitive assessment					X	X
	**Sensorimotor assessment**	Trunk Control Test	X	X	X	X		
		Modified Ashworth scale		X	X	X		
		Functional Oral Intake Scale		X	X	X	X	X
	**Disability level**	Early rehabilitation Barthel Index	X	X	X	X		
		Disability Rating Scale		X	X	X		
		Functional improvement measure		X	X	X		
		Glasgow Outcome Scale-expanded	X	X	X	X	X	X
	**Participation level**	Community I Questionnaire					X	X
		Electroencephalography		X	X			
**Neurophysiological evaluation**		Somatosensitive Evoked potential		X				
		Motor-evoked potential		X	X			
		Electromyography		X	X			
		ApoE		X	X	X		
**Genetic markers**		Brain-derived neurotrophic factor		X	X	X		
		Dopamine receptor 2		X	X	X		

***Legend:** Clinical complications: metabolic, cardiovascular, muscular and skin, gastrointestinal, genitourinary, respiratory, epilepsy or myoclonus, neurosurgery compliances, POA, PHS*.

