### Outcome Measures

The primary outcome is the functional recovery, given by the achievement of a moderate functional disability (GOS-E>4), whereas the independent variables will be the severity of the patients' clinical state at admission. For those patients who will remain in DoC at discharge from the IRU, given that the GOS-E does not allow accurate discrimination between different states of consciousness, consciousness improvement will be considered. The improvement will be stated as the transition from one state of consciousness to a higher one (based on the CRS-R assessment). These outcomes will be measured both at short-term evaluations, T1 and T2, and at long-term ones, T3 and T4.

Secondary outcomes will be considered at the same time points. They are (1) tracheostomy decannulation success and its timing and (2) complete oral feeding recovery corresponding to FOIS score ≥4. Additionally, at follow-up time points (T3 and T4), the level of participation, using the CIQ scale, and the subjective and caregiver perceived QoL, using the QoLibri, will also be considered as secondary outcomes.

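### The consciousness-improvement outcome is defined by the CRS-R at T3 and T4, but those contacts are telephone interviews, so it cannot be obtained there by its own rule or read as one series with T0 to T2

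*Protocol article*

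**What the plan says.** Outcome Measures gives the reason for a second outcome in patients who remain in DoC at discharge: "given that the GOS-E does not allow accurate discrimination between different states of consciousness, consciousness improvement will be considered". It then defines that outcome: "The improvement will be stated as the transition from one state of consciousness to a higher one (based on the CRS-R assessment". The timing follows: "These outcomes will be measured both at short-term evaluations, T1 and T2, and at long-term ones, T3 and T4".

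Clinical Evaluation sets out how the scale is given. Consciousness measures are "administered by skilled members of the multiprofessional team, will be recorded at each time point". For the CRS-R in particular: "The best score obtained from five administrations performed in seven days will be recorded". No exception is made for any visit.

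The same section describes the long-term contacts differently: "After hospital discharge, at T3 and T4, a phone interview with the patients and their principal caregiver will be carried out". Consciousness level is listed among the things this interview evaluates, but no instrument for it is named. In Table 1 the row "Coma Recovery Scale revised" is ticked at T0, T1, T2, T3 and T4, and the last two columns stand under the phone follow-up heading.

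**The concern.** A CRS-R state is the result of repeated bedside examination. A patient without functional communication cannot be interviewed by telephone, so at T3 and T4 the caregiver would have to be the main source. If the state recorded then is treated as a CRS-R state, an apparent transition between T2 and T3 can come from real recovery or from the switch in how the state was determined, and the two cannot be separated.

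This outcome sits in the primary-outcome paragraph, and T3 and T4 are the whole of its long-term part. The state recorded there would also feed two later steps. One is the over-time test that Statistical Analysis plans for variables measured at every visit. The other is the long-term prediction modelling, for which the Discussion names recovery of consciousness as a milestone.

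**Working it through.** No figure in the article depends on this point. The sample size rests on GOS-E, and it reproduces without using the CRS-R, with n = z²p(1−p)/d² and z = 1.96:

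- UWS: p = 0.03, d = 0.03 gives 124.2, rounded up to 125 (stated: 125).
- MCS: p = 0.47, d = 0.05 gives 382.8, rounded up to 383 (stated: 384).

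The check on the concern itself is a comparison of the article's own statements.

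| Element | T0, T1, T2 | T3, T4 | Source |
|---|---|---|---|
| Outcome for patients still in DoC at discharge | CRS-R state transition (T1, T2) | CRS-R state transition | Outcome Measures |
| CRS-R ticked | yes | yes | Table 1 |
| Assessor | skilled staff | skilled staff (stated for every time point) | Clinical Evaluation |
| Number of administrations | five in a week, best kept | same rule, no exception | Clinical Evaluation |
| Mode of contact | in person (inferred: blood samples and the Trunk Control Test are scheduled at T0, T1 and T2) | telephone, patient and caregiver | Clinical Evaluation, Data Collection, Table 1 |
| Remote version of the CRS-R | not needed | none named | Clinical Evaluation |

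1. **Can the rule be met by phone?** The Introduction separates the states by signs such as visual search and a localized motor response to a painful stimulus. These have to be elicited and observed. A phone conversation with a caregiver does neither, and it is not five administrations by trained staff.

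2. **Might a phone version be implied?** For cognition the article does name a phone form, of the Montreal Cognitive Assessment. For consciousness it names only the Italian version of the CRS-R.

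3. **How much of the outcome is affected?** The outcome has four time points (T1, T2, T3, T4). Two of the four, and both long-term ones, fall under phone follow-up.

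4. **Does the analysis keep them apart?** Statistical Analysis sends variables measured at all time points to a repeated-measures ANOVA or a Friedman test. With five ticks in Table 1 the CRS-R qualifies, so three examined values and two phone-derived values would enter one test.

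5. **Is there another safeguard at T3/T4?** The Discussion plans to combine the CRS-R with EEG patterns for a more accurate diagnosis. Table 1 schedules EEG at T0 and T1 only, so it cannot support the state recorded by phone.

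**The case against.** The strongest reply is that this is a condensed article. The T3/T4 paragraph speaks only of consciousness level and does not itself mention the CRS-R. Tool references are in Supplementary Table S1, which is not shown, and that table or the full protocol might cite a remote procedure. This stands in part: it cannot be asserted that staff will in fact enter a caregiver's impression under a CRS-R label. It does not remove the conflict. The article itself states the instrument, the administration rule, the time points and the mode of contact, and these disagree.

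A second reply is that bedside diagnosis is itself imperfect, so T0 to T2 is no error-free reference. That is true, and the Discussion says so. The problem is the change of method partway through the series, which remains even if both methods err.

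A reader might go further and use the Discussion's figure of up to 40% misclassification as an error rate for phone reports. The documents do not support this. The figure concerns clinical diagnosis, gives no direction, and says nothing about telephone or caregiver report. Caregivers could over-report as well as miss signs. Moreover, an unchanged patient wrongly recorded as worse still counts as not improved, so that kind of error leaves this outcome unchanged. Only missed or false improvements matter, and no figure for either is given.

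A reader might also infer that the primary outcome as a whole is compromised. It is not: GOS-E>4, on which the sample size rests, and the CRS-R outcome at T1 and T2 are outside this argument.

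**Conclusion.** The concern holds as an internal contradiction in the current text. For patients still in DoC at discharge, the CRS-R transition cannot be obtained by its own rule at T3 and T4. Change from T0-T2 to T3/T4 would confound true change with method, informant and number of assessments.

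The extent is two of four time points, in one subgroup. The article does not say how many patients are expected to be in that subgroup or to survive to T3 and T4. The non-comparability is inferred from the change of mode, and the documents give neither its size nor its direction.

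The conclusion assumes that T1 and T2 are assessed face to face and that no remote CRS-R procedure is specified elsewhere. If one is, the five-administration rule and the phone mode would still have to be reconciled here.

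**What to change.** Reconcile Clinical Evaluation, Table 1 and Outcome Measures as follows:

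- Limit the CRS-R-defined transition to the time points assessed face to face, T1 and T2, and remove the CRS-R ticks at T3 and T4.
- Define for T3 and T4 a separately named, coarser outcome reported by phone or caregiver. One example is whether functional yes/no communication has been regained, which the Introduction already uses to mark emergence from MCS. Analyse and report it apart.
- Keep T3 and T4 out of the CRS-R repeated-measures test and out of any prediction target labelled as CRS-R.
- Do not rely on a GOS-E split (2 versus 3 or more) alone as the replacement, since Outcome Measures itself says GOS-E does not discriminate states of consciousness accurately.

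The cost is wording and labelling in the analysis, with no extra visits. The price is that no CRS-R-based transition between UWS, MCS− and MCS+ is available at 12 and 24 months. The long-term outcome also still rests on caregiver report, now labelled as such. If the CRS-R transition is wanted at those times, the protocol would have to specify an in-person assessment, at the cost of further visits, or a named remote procedure analysed as a separate measure.
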